### 7.3. Secondary outcomes - ordinal

Modified Rankin score at twelve-months will be examined in its full format [scores of 0,1,2,3,4,5,6] using the methods described for the primary outcome.

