## 2. Introduction

Fluoxetine Or Control Under Supervision (FOCUS) is a parallel-group multicentre randomised trial to establish the effect(s) of routine administration of Fluoxetine in patients with a recent stroke. The trial aims to recruit at least 3000 patients. Patients are randomised via a web based randomisation system utilising a minimisation algorithm with a random component to receive Fluoxetine 20mg once daily or matching placebo capsules for 6 months and follow up at 6 and 12 months.

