## 3. Statistical methods from protocol

Our primary analyses will retain patients in their original assigned treatment groups.

Our primary analysis will compare the mRS at the six month follow up using an ordinal analysis adjusted for any baseline imbalance in those factors included in our minimisation algorithm.

We will compare the mRS at the twelve month follow up to establish if any benefits observed at 6 months are maintained.

Secondary analyses will compare the two treatment groups with respect to the following outcomes at 6 and 12 months.

- Survival (Logistic regression)
- EQ5D-5L (HRQOL) to generate utilities
- SIS (for each of 9 domains on which the patient scored 0-100)
- MHI 5 (mood)
- Fatigue (Vitality subscale of SF36)
- New diagnosis of depression requiring treatment with antidepressants
- Adverse events
- Adherence to trial medication

Longer term survival will be analysed with Cox proportional hazards model

We will also perform analyses of potential mediating factors e.g. the role of depression. We will seek to answer the question whether any benefits are mediated by improvement in mood (based on MHI 5 and also whether any apparent loss of benefits in mRS or SIS between 6 months to 12 months is because of a deterioration in mood.

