### 5.1.3. Missing Data

mRS includes death so it is expected that the number with missing mRS at follow up will be minimal. Anyone with missing mRS will not be included in any analysis requiring mRS (complete case analysis).

For the quality of life measures [SF-36, EQ5D, MHI-5, SIS] we will present results for those who are alive at follow up and any discrepancy in death rates between groups will be taking into account in the interpretation. Missing data for single questions within scores will handled as detailed by each scoring method, where responses to all questions within a scale are missing that patient will not be included in that part of the analysis. If required due to amount of patients with missing scores a sensitivity analysis may be performed.

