## 7. Final analysis

### 7.1. Primary outcome

Comparison of Modified Rankin score [mRS] at six-months post randomisation by treatment group where mRS treated in its full ordinal format [scores of 0,1,2,3,4,5,6]. This will be examined using an ordinal logistic regression and will be performed in both an unadjusted manner and also adjusted for factors in the baseline minimisation (as recommended by the Draft CPMP guidelines, December 2001). We will present common odds ratios using the proportional odds method and for the unadjusted analysis we will also present the individual dichotomies.

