### 7.6. Pre-specified sub group analysis

Comparison of mRS at 6-months based on Ordinal analysis will be split by the following sub-groups: age [<70, ≥70], baseline probability of being alive and independent at 6-months [<0.15, 0.16-1 based on Carls model], type of stroke [ischaemic, haemorrhagic], patient able to provide own consent [yes, no] adjusting for baseline motor impairment [yes/no], baseline aphasia [yes/no] and baseline depression [yes/no].

Motor impairment: In patients with motor impairment resulting from the initial stroke [where motor impairment is defined as above] is there a difference in the motor function at 6 months [as measured by SIS, question 12, 17, 18 on follow up)]. Is this maintained at 12 months? Linear regression analysis will be performed on the baseline to 6-month change and separately for the 6-month to 12-month change both unadjusted and also adjusted for factors in the minimisation.*.*

Communication impairment: In patients with communication impairment resulting for the initial stroke [where communication impairment is defined as above on NIHSS] is there a difference in the communication function at 6 months [as measured by SIS, question 15]. Is this maintained at 12 months? This analysis will be performed unadjusted and also adjusted for factors in the minimisation.

Linear regression analysis will be performed on the baseline to 6-month change and separately for the 6-month to 12-month change both unadjusted and also adjusted for factors in the minimisation.

Mood: Is there a relationship between outcome [as defined by mRS at 6-months] and mood [measured using MHI5] and is this relationship affected by Fluoxetine?

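### The SAP asks whether a 6-month mRS benefit is maintained at 12 months but never estimates the change in the mRS treatment effect between the two visits

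*SAP*

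**What the plan says.** Patients receive fluoxetine or "matching placebo capsules for 6 months and follow up at 6 and 12 months" (section 2), so the 12-month visit falls about six months after the end of trial treatment.

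Section 3 states the purpose of the later mRS comparison: "We will compare the mRS at the twelve month follow up to establish if any benefits observed at 6 months are maintained".

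Section 7.3 carries this out as follows: "Modified Rankin score at twelve-months will be examined in its full format", and this is done "using the methods described for the primary outcome". Under section 7.1 that means ordinal logistic regression, unadjusted and adjusted for the minimisation factors: "We will present common odds ratios using the proportional odds method".

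Section 7.6 poses the same question of maintenance for SIS function in patients with motor or communication impairment, and there it adds an analysis of change: "Linear regression analysis will be performed on the baseline to 6-month change and separately for the 6-month to 12-month change".

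On missing data, section 5.1.3 says: "Anyone with missing mRS will not be included in any analysis requiring mRS (complete case analysis"). It also expects few missing mRS values, because death is a category of the scale.

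**The concern.** Whether a benefit is maintained is a question about how the treatment effect at 12 months relates to the effect at 6 months. The 12-month odds ratio alone answers a different question, namely whether there is an effect at 12 months. For mRS the SAP has no arm-by-visit term, no contrast of the two odds ratios and no statement of what counts as maintained. Section 3 also plans to ask whether an apparent loss of mRS benefit is explained by mood, so it would explain a change that nothing in the plan estimates.

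The two odds ratios come largely from the same patients and are correlated. Laying their confidence intervals side by side therefore gives no valid interval for the change. With no criterion fixed in advance, the conclusion could be chosen after both results are known, and the easiest informal reading is by significance at each visit. That reading can make a constant effect look lost and a partly faded one look kept.

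**Working it through.** The SAP gives no effect size, power, mRS distribution or between-visit correlation, so there is no stated figure to reproduce. What follows is an illustration.

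**Inputs**
- From the SAP: "The trial aims to recruit at least 3000 patients" (section 2); taken as N = 3000, 1:1.
- Assumed: mRS 0 to 6 proportions 0.08, 0.16, 0.14, 0.30, 0.08, 0.14, 0.10; true common odds ratio (OR) 1.15 to 1.30; correlation ρ of 0.6 to 0.9 between the 6- and 12-month estimates; two-sided 5% level; the same patients at both visits.

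**Step 1: precision at one visit.** V = N(1 − Σp³)/12, with Σp³ = 0.0386. So V = 3000 × 0.9614/12 = 240.3 and SE(log OR) = 1/√240.3 = 0.0645. At OR 1.20, log OR = 0.1823, the expected z is 0.1823/0.0645 = 2.83, and power is 81%.

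**Step 2: what reading by significance would do.** The two z statistics are taken as bivariate normal with correlation ρ. Both probabilities are conditional on significance at 6 months, and the ranges cover ρ = 0.6 to 0.9.

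| True 6-month OR | Power at 6 months | Constant effect, not significant at 12 months | Log OR halved, still significant at 12 months |
|---|---|---|---|
| 1.15 | 58% | 12% to 25% | 29% to 33% |
| 1.20 | 81% | 6% to 12% | 35% to 36% |
| 1.25 | 93% | 2.5% to 5% | 44% |
| 1.30 | 98% | about 1% | 54% |

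A simulation of 3000-patient trials with rank tests agrees at OR 1.20: 8% to 9% in the third column and 36% to 37% in the fourth, with correlation of the statistics about 0.76 to 0.86. With 10% fewer patients at 12 months, the third column at OR 1.20 becomes 9% to 16%. An effect that has vanished completely would be significant at 12 months in only about 3% to 4% of trials (OR 1.15 or 1.20), so the risk of wrongly calling it maintained concerns partial fading.

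**Step 3: what a direct contrast would give.** SE of the log ratio of odds ratios = 0.0645 × √(2(1 − ρ)). The 95% CI multiplies and divides the ratio by exp(1.96 × SE). Halving at OR 1.20 is a change of 0.1823/2 = 0.0912 on the log scale, a factor of about 1.095.

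| ρ | SE | 95% CI factor | Power to detect halving at OR 1.20 |
|---|---|---|---|
| 0.6 | 0.058 | 1.12 | 35% |
| 0.75 | 0.046 | 1.09 | 52% |
| 0.8 | 0.041 | 1.08 | 61% |
| 0.9 | 0.029 | 1.06 | 89% |

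Treating the two odds ratios as independent would give SE = 0.0645 × √2 = 0.091 and a factor of exp(1.96 × 0.091) = 1.20. That is wider than any row of the table, which is why two separately reported intervals cannot stand in for the contrast.

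**The case against.** The strongest reply is that the SAP contains no wrong rule. A reader might infer that it will call a benefit maintained if the 12-month result is significant and lost if it is not. No section says so, so the error rates in Step 2 describe one possible reading and not a consequence of the plan. Both odds ratios will be reported and can be compared informally. This stands, and it limits the point to a missing contrast and criterion.

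Maintained can also be read as still present at 12 months, which the randomised 12-month comparison answers directly. That reading is fair and is why the stand-alone odds ratio should stay. It does not cover a loss of benefit between visits, which section 3 itself raises and section 7.6 analyses for SIS.

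A reader might also infer that different patients in the two complete-case sets would pass for a change in effect. The documents do not support giving that much weight, since section 5.1.3 expects few missing mRS values.

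The SIS analysis is only a partial precedent: it is linear regression on 0 to 100 scores in subgroups and does not transfer directly to an ordinal scale that includes death. It shows that the question was recognised, not which model to use.

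Finally, the contrast is not highly precise for this purpose. At ρ = 0.6 or 0.75 its interval could often not separate full retention from loss of half the effect. That is true, but the interval would show the uncertainty, which the present plan leaves unquantified.

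**Conclusion.** The concern holds in a limited form. Section 3 sets a maintenance objective for mRS, section 7.3 delivers only a second cross-sectional comparison, and no section estimates the change in treatment effect on this scale. If the two results were read by significance, at an OR of about 1.20 a constant effect would look lost in about 6% to 12% of trials significant at 6 months, and a halved log odds ratio would remain significant in about 36%. False loss falls to about 1% at OR 1.30, where the second figure rises to 54%. The effect sizes, mRS distribution and correlations are all assumptions.

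The objective is secondary. The primary 6-month analysis and the 12-month effect estimate are unaffected, so this is a cheap improvement and not a defect in the main result.

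**What to change.** In section 7.3, keep the stand-alone 12-month common odds ratio and add:

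1. The ratio of the 12-month to the 6-month common odds ratio with 95% CI, in patients whose mRS (including death) is known at both visits.
2. The method: a joint proportional-odds model with arm, arm-by-visit, the minimisation factors and cutpoints specific to each visit, clustered by patient. A patient-level bootstrap of the two fitted models would also serve. Visit-specific cutpoints matter because death is absorbing and accumulates while survivors may move either way, so a single visit shift across all cutpoints is doubtful.
3. A statement that maintenance is judged from the 12-month effect together with this ratio and its interval, and that an interval including 1 does not by itself show full maintenance.

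The cost is SAP wording and one further analysis of data already scheduled. The downside is one more secondary estimate, with limited power to detect partial fading if the between-visit correlation is low.

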### 7.4. Secondary outcomes - continuous

Where the outcome of interest is continuous, these will be compared between treatment groups using linear regression adjusting for factors in the baseline minimisation, or an alternative approach as necessary. This analysis will be conducted for the following outcomes at both six and twelve months.

1. Quality of life as measured by the EuroQol [EQ-5D]
2. Depression and anxiety as measured by the mental health inventory 5 [MHI-5 – question 21,22 of 6-month follow up; question 17,18 of 12-month follow up] and SIS [question 14 on 6-month follow up; question 10 on 12-month follow up].
3. Fatigue as measured by the vitality sub-scale of the Short Form (36) Health Survey [SF-36 question 20 on 6-month follow up; question 16 on 12-month follow up].
4. Limb strength as measured by SIS [question 12 on 6-month follow up; question 8 on 12-month follow up].
5. Hand function as measured by SIS [question 18 on 6-month follow up; question 14 on 12-month follow up].
6. Cognitive function as measured by SIS [question 13 on 6-month follow up; question 9 on 12-month follow up].
7. Communication as measured by SIS [question 15 on 6-month follow up; question 11 on 12-month follow up].
8. Extended ADL as measured by SIS [question 16 on 6-month follow up; question 12 on 12-month follow up].
9. Mobility as measured by SIS [question 17 on 6-month follow up; question 13 on 12-month follow up].
10. Social activity as measured by SIS [question 19 on 6-month follow up; question 15 on 12-month follow up].
11. Overall patient outcome as measured by the SIS total score
12. Overall recovery as measured by SIS thermometer [question 28 on 6-month follow up; question 24 on 12-month follow up].

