### 4.2. Study Assessments

|  | Days | Weeks | | | | | | | |
| --- | --- | --- | --- | --- | --- | --- | --- | --- | --- |
| **Assessment** | 2-15 | 4-6 | 12 | 24 | 26 | 30 | 50 | 52 | 54 |
| ***Local*** |  |  |  |  |  |  |  |  |  |
| Screen of eligibility | x |  |  |  |  |  |  |  |  |
| Check results of post stroke bloods | x |  |  |  |  |  |  |  |  |
| Give PIB to patient and/or carer | x |  |  |  |  |  |  |  |  |
| CONSENT | x |  |  |  |  |  |  |  |  |
| Collect baseline data | x |  |  |  |  |  |  |  |  |
| Randomise | x |  |  |  |  |  |  |  |  |
| Record treatment code/study no. | x |  |  |  |  |  |  |  |  |
| Prescribe study medication | x |  |  |  |  |  |  |  |  |
| Dispense 6 months of treatment | x |  |  |  |  |  |  |  |  |
| FAX no. of dispensed medication | x |  |  |  |  |  |  |  |  |
| Complete discharge form including |  | + |  |  |  |  |  |  |  |
| Adverse events |  | + |  |  |  |  |  |  |  |
| All medications |  | + |  |  |  |  |  |  |  |
| Adherence |  | + |  |  |  |  |  |  |  |
| Updated contact details |  | + |  |  |  |  |  |  |  |
| ***Central (postal or telephone)*** |  |  |  |  |  |  |  |  |  |
| Email/fax notification of allocation | x |  |  |  |  |  |  |  |  |
| Letter informing GP of participation | x |  |  |  |  |  |  |  |  |
| 1 month follow up for outpatients |  | o |  |  |  |  |  |  |  |
| 3 month prompt to patients |  |  | x |  |  |  |  |  |  |
| GP Questionnaire |  |  |  | x |  |  | x |  |  |
| Adverse events |  | o |  | x |  |  |  |  |  |
| Follow up on previous AEs |  |  |  | x |  |  | x |  |  |
| All medications |  | o |  | x |  |  | x |  |  |
| Adherence |  | o |  | x |  |  |  |  |  |
| Resource use |  |  |  | x |  |  | x |  |  |
| Patient follow up |  |  |  |  |  |  |  |  |  |
| Adverse events |  | o |  |  | x |  |  |  |  |
| Follow up on previous AEs |  |  |  |  | x |  |  | x |  |
| Adherence |  | o |  |  | x |  |  |  |  |
| modified Rankin scale |  |  |  |  | x |  |  | x |  |
| Stroke Impact Scale |  |  |  |  | x |  |  | x |  |
| Mental health inventory 5 |  |  |  |  | x |  |  | x |  |
| EQ5D-5L (HRQOL) |  |  |  |  | x |  |  | x |  |
| SF36 Vitality subscale |  |  |  |  | x |  |  | x |  |
| Resource use |  |  |  |  | x |  |  | x |  |
| Retrieve residual capsules (pill count, reconciliation and destruction) |  |  |  |  | x |  |  |  |  |

+ - only for patients enrolled as inpatients

o - only for patients enrolled as outpatients

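### Each continuous score is compared visit by visit among responders only, so a living patient's score at one visit does not inform the comparison at the other; a joint model per scale would use it at little cost.

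*SAP*

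**What the plan says.** Section 7.4 compares continuous outcomes between arms "using linear regression adjusting for factors in the baseline minimisation, or an alternative approach as necessary", and then: "This analysis will be conducted for the following outcomes at both six and twelve months". It names no model that takes the two visits together and does not say when an alternative would be needed or what it would be.

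Section 5.1.3 governs missing scores on these scales. Results are for survivors: "we will present results for those who are alive at follow up and any discrepancy in death rates between groups" is left to interpretation. Gaps within a scale follow the instrument's own rule ("Missing data for single questions within scores will handled as detailed by each scoring method"). For a wholly missing scale, "where responses to all questions within a scale are missing that patient will not be included in that part of the analysis". Finally, "If required due to amount of patients with missing scores a sensitivity analysis may be performed", with no threshold, method or assumption.

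The schedule in section 4.2 marks the SIS, MHI-5, EQ5D-5L and SF36 vitality subscale at weeks 26 and 52 only, with nothing at days 2-15. Follow-up is postal or by telephone.

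**The concern.** Without a baseline value, the score at the other visit is probably the best available predictor of a missing score on the same scale. The plan collects it but does not use it for that purpose. The adjustment rests on four two-level minimisation factors, which can explain only part of why a patient after a stroke fails to return a form.

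Two things are at stake, mainly at 12 months. Some precision is lost. And if non-response depends on health in a way that differs between arms, the responder-only treatment difference is biased, although data that would reduce the bias are in hand.

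Persistence of effect is one of the plan's own questions: sections 3 and 7.6 ask whether benefit at 6 months is maintained at 12. Two separate regressions compare a 6-month effect in one set of responders with a 12-month effect in another, so a change in who responds can be mistaken for a change in effect.

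**Working it through.** **Reading the sections together.** Section 7.4 gives one regression per score and visit. Section 5.1.3 removes a patient only from the part of the analysis where the scale is missing. A patient with a 6-month score alone is therefore in the 6-month regression and absent from the 12-month one.

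**Inputs.** The SAP gives no SD, between-visit correlation or non-response rate for these scales, so there is no planned figure to reproduce. From the SAP: at least 3,000 patients, about 1,500 per arm. Assumed: n = 1,300 alive per arm, SD = 25 on a 0-100 scale, correlation r = 0.7 (r² = 0.49), all patients have 6-month scores and a fraction m lack the 12-month score. The odds of 12-month non-response double for each SD worse at 6 months.

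**Precision, same non-response in both arms.** If scores are missing at random, the variance of the 12-month difference under a joint model, relative to the single-visit regression, is 1 − m·r². The reduction is:
- m = 5%: 0.05 × 0.49 = 2.5%
- m = 10%: 4.9%
- m = 20%: 9.8%

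If non-response depends on health as assumed, responders vary less at 6 months. Let v be their 6-month variance relative to all patients: numerical integration gives 0.979, 0.962 and 0.937 at m = 5%, 10% and 20%. The variance ratio is then [r² + (1 − r²)/(1 − m)] ÷ {[r²·v + 1 − r²]/(1 − m)}. At m = 10% this is (0.49 + 0.51/0.90) ÷ [(0.49 × 0.962 + 0.51)/0.90] = 1.057 ÷ 1.090 = 0.969, a reduction of 3.1%. At 5% and 20% the reductions are 1.4% and 6.9%. In terms of the standard error, the range is about 0.7% to 3.5%. The 6-month comparison gains nothing under this pattern; it gains only where a patient has a 12-month score but no 6-month one.

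**Bias, non-response differing between arms.** Let μ(m) be the mean standardised 6-month score of responders. Integration gives μ = 0.0662, 0.0789, 0.0915 and 0.1040 at m = 10%, 12%, 14% and 16%. The bias in the 12-month difference from the single-visit regression is SD × r × [μ(m₁) − μ(m₂)], with SD × r = 17.5:

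| Non-response | Bias (points) | Standard error | Bias / SE | Actual error of a nominal 5% test |
|---|---|---|---|---|
| 12% v 10% | 17.5 × 0.0127 = 0.22 | 1.03 | 0.22 | 5.5% |
| 14% v 10% | 17.5 × 0.0253 = 0.44 | 1.03 | 0.43 | 7.1% |
| 16% v 10% | 17.5 × 0.0378 = 0.66 | 1.04 | 0.64 | 9.8% |

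Simulation of the same settings gives 0.24, 0.46 and 0.67 points for the single-visit regression and about zero for the joint estimate. With equal rates and equal dependence on health in both arms, both estimates are unbiased apart from simulation error.

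**A less favourable mechanism.** If non-response depends on the unseen 12-month score instead, with the same doubling of odds and 16% v 10%, the single-visit bias is 25 × 0.0378 = 0.95 points. The joint estimate, by simulation, has a bias of 0.49 points, so about half remains.

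**The case against.** Separate adjusted regressions at two fixed visits are a legitimate choice, and the SAP contradicts nothing by making it. It also foresees an alternative approach and a sensitivity analysis for missing scores. Patients and assessors are blinded and treatment stops at 6 months, so a gap of 4 to 6 percentage points in 12-month response between arms is not something the SAP leads one to expect. At 12% v 10% the effect on a test is slight. The joint model looks clean in the main calculation because non-response was generated from the 6-month score, which is exactly what that model assumes. These are secondary outcomes, and the assured gain in standard error is a few per cent at most.

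Most of this stands, and it limits the size of the point. What does not stand is the comfort drawn from the two open clauses: neither has a trigger or a method, so both could be settled after the data are seen. Patients missing both forms are not helped by either approach, since section 4.2 shows no baseline score. (Section 7.6 speaks of change from baseline on the SIS; the schedule is followed here.)

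A reader might infer that a 6-month score is thrown away when the 12-month form is missing. The SAP does not support that: section 5.1.3 omits the patient only from the part where the scale is missing. A reader might also infer that the 12-month results must be biased whenever sicker patients respond less. That is not so either: under the assumptions above, bias in the treatment difference requires non-response to differ between arms, in its rate or in its link with health.

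**Conclusion.** The point holds as an inexpensive improvement to the secondary analyses; the planned method is not invalid. The plan leaves a known predictor of the missing score unused and fixes no missing-data method for these scales. The loss is about 1-7% of variance at 12 months for 5-20% health-related non-response. The possible bias is about 0.2-0.7 points (0.01-0.03 SD) for 12-16% v 10%. All of these sizes rest on the assumed SD, correlation, number alive and non-response, none of which the SAP states. In every setting examined the joint estimate was about as good as the single-visit estimate or better, but it is only a partial remedy if non-response depends on the unseen score.

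**What to change.** In section 7.4, for each scale, specify a repeated-measures linear model with visit, treatment-by-visit, minimisation factors-by-visit and an unstructured covariance, and report the treatment difference at each visit. Take the 6-month contrast from a fit to patients alive at 6 months and the 12-month contrast from a fit restricted to patients alive at 12 months. This keeps the survivors-only rule of section 5.1.3 and ensures that no score is implied after death. Keep the single-visit regression as the named sensitivity analysis, in place of the optional one in 5.1.3.

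The cost is SAP wording and slightly more programming (two fits per scale). The model assumes that scores are missing at random given the other visit's score and the covariates, which should be stated, together with the fact that it cannot help patients missing both visits.
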